#### Cost-Effectiveness Analysis

Cost-effectiveness analysis and incremental cost-effectiveness analysis will be performed, and the incremental cost for every additional beneficiary attending the VC will be calculated. To calculate the increase in the number of patients, the average number of patients visiting per day during the same months in the previous year will be subtracted from the average in the study period. A change in the control VCs, if any, will be further deducted from this before using this as the denominator for calculating cost-effectiveness.

### Outcomes

The primary outcome for this study will be an increase in the number of walk-in patients at the VCs from baseline (7-8 walk-in patients to 14 per day after the intervention period of 4 months). The secondary outcomes will be uptake of spectacles and uptake of surgery among those advised. If the intervention proves effective in terms of the number of people visiting the VCs, cost-effectiveness will also be a secondary outcome.

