### Sample Size

The average OPD attendance at the intervention centers is 7 per day at present. We expect to achieve 14 after the intervention, failing which, the intervention will not be considered a success. Therefore, the primary objective of the statistical analysis would be to estimate the average attendance, postintervention, with extreme precision, which will lead us to assess whether we have been able to achieve the target (14 per day, on average). We set the confidence interval (CI) to ±1 for the postintervention sample mean (the narrowest-possible CI in this case). To check whether at least 20 per day on average has been achieved, we expect a sample mean of at least 21 (ie, the CI will be 20-22). The number 20 has been determined based on a feasibility study conducted to project VC sustainability. We assume that the probability of the CI is 95% and the daily OPD attendance has a Poisson distribution. Thus, we expect that the postintervention daily attendance will have a Poisson distribution with a mean of at least 21. This implies that the variance of the distribution will also equal 21 (or more), and we want to estimate the mean with a 95% CI of ±1. This requires a minimum sample size of 81 days.

We used the following formula to calculate the sample size:

Sample size = (1.96^2^/*d*^2^) × Variance of the distribution

where 1.96 is the 97.5 percentile point of the standard normal distribution and d is the length of the CI (on one side of the estimate). If d = 1 and variance = 21, we obtain sample size = 81. We set a target of 20 per day in the pre-CODIV-19 time, but due to the pandemic, we revised our desired target to 14 per day to consider the intervention a success. We persisted with the additional days in the sample size (instead of 58 days for a target of 14) to be able to estimate up to 14 per day OPD attendance with precision.

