Any person with a visual acuity of <6/12 (cutoff) or other eye issues will be counseled and referred for a comprehensive examination to the VC. A referral slip will be provided to the patient when referred, mentioning the reason for referral. Referred patients’ records will be accessible to the vision technician (optometrist) through the software. Patients reporting to the VC for a comprehensive checkup and treatment, due to the door-to-door intervention, will be recorded using vision center management software (VCMS). Any patient requiring surgical treatment or further care will be referred to the respective secondary center. Free cataract services will be provided to patients unable to afford the same. Follow-up of referred patients will be performed by the coordinators in the field.

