### Control Arm

The control arm VC will continue its routine awareness activities and health talk sessions in the community. The VC attendant will prepare a monthly activity plan and organize activities in the surrounding 8-10 villages. Persons with eye issues will be recorded and referred to the VC for further evaluation and treatment. Patients reporting to the VC will be registered in the VCMS. For surgical intervention or further care, patients will be referred to the respective secondary center. Follow-up of referred patients will be performed by the coordinators in the field.

A comparison of the activities of the community health workers in the two arms is summarized in Table 1. The activities will be the same in both the arms and will also be standardized in the same manner; only their mode and reach will be different.

**Table 1 table1:** Comparison of activities of community health workers in the two study arms.

Serial number	Activity	Intervention arm	Control arm
1	Meeting with key stakeholders	Yes	Yes
2	Health talk sessions in community Refer patients to VC	No	Yes
3	Awareness activity through IEC distribution	Yes (door-to-door)	Yes (cluster meeting in village during visits)
4	Permission for door-to-door survey intervention	Yes	No
5	Door-to-door screening Refer patients to VC	Yes	No

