### Data Collection, Management, and Analysis

#### Data Collection and Variables

We will collect both electronic and manual data for both study arms. In the intervention arm, field-level data (door-to-door surveys) will be captured through software, while field-level activity in the control arm will be manually recorded in the activity register. VC-level data will be extracted from the VCMS, which will contain data for both control and intervention VCs. In both arms, programmatic data will be collected, which will include data of the villages screened, door-to-door screening, walk-in OPD visits, those reporting after referrals from the field, and spectacles advised and their uptake, as well as referrals for cataract, specialty, and surgical follow-up (Figure 1 and Multimedia Appendix 1). Cost data will be collected for direct, indirect, and opportunity costs, such as rent, human resources, overheads, and community activities (Multimedia Appendix 2). We will also collect data for revenue from the OPD, spectacles, and surgeries done.

Most of the data for analysis will be directly extracted from the existing software at the VCs. The rest of the data pertaining to the cost will be entered, collected, and monitored as part of regular processes in the field. This will make the data collection process streamlined and integrated into the regular operations. Although the costs incurred in running any program may vary for different providers, we feel that the detailed checklists will help in disaggregating that data for use by different service providers.

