## Discussion

### Importance of Principle Findings

To the best of our knowledge, there is no previous study assessing the impact of door-

to door intervention on the sustainability of VCs. VCs are evolving as an important model for primary eye care [7,10,19]. Any such model needs to be sustainable for it to be universally adopted. Uptake of glasses and uptake of surgery by patients are the major contributors to the sustainability of these VCs [24]. Both these parameters are dependent on the number of patients visiting the VC, and that will be assessed in our study.

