### Addressing the Barriers to Uptake of Services

In their study describing barriers to the uptake of eye care services among the rural population, Marmamula et al [17] reported a lack of felt need as the most important person-related barriers. Thus, when designing our intervention package, we have included awareness generation as one of the key components. Other barriers detected in that population are the absence of someone to accompany, lack of accessibility, and affordability. Taking the preliminary screening to people’s doors in our intervention should manage, to some extent, the barriers to accessibility and the absence of an accompanist. We have also made the first examination at the VCs, free of cost for those reporting after a preliminary screening.

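### The secondary uptake outcomes are conditional on being advised, a group formed after allocation that the intervention is designed to enlarge and change, so a between-arm difference is not protected by randomisation

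*Protocol article*

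**What the plan says.** The Outcomes section defines the secondary outcomes in one sentence: "The secondary outcomes will be uptake of spectacles and uptake of surgery among those advised". The primary outcome beside it is a rise in walk-in patients, "7-8 walk-in patients to 14 per day after the intervention period of 4 months". The Sample Size section gives the starting level: "The average OPD attendance at the intervention centers is 7 per day at present".

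The arms differ in how people reach the VC. In the intervention arm an attendant measures acuity household by household, and "Any person with a visual acuity of <6/12 (cutoff) or other eye issues will be counseled and referred for a comprehensive examination to the VC". The Discussion, on barriers to uptake, adds: "We have also made the first examination at the VCs, free of cost for those reporting after a preliminary screening". It also names lack of felt need as the leading person-related barrier and gives this as the reason for including awareness generation. For the other arm, "The control arm VC will continue its routine awareness activities and health talk sessions in the community". Control attendants also record people with eye problems in the villages and refer them.

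Other sections touch on uptake without this condition. The abstract lists spectacle and surgery uptake among the primary outcomes, and uptake of refraction correction among the secondary ones, with no denominator. Data Collection and Variables lists "spectacles advised and their uptake", so both numerator and denominator will be recorded. Data Analysis plans change from baseline in walk-ins, referrals, service uptake and costs, in wording that fits either counts or proportions.

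On why uptake matters, the Discussion says: "Uptake of glasses and uptake of surgery by patients are the major contributors to the sustainability of these VCs". It then adds that both depend on how many patients attend.

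**The concern.** Randomising VCs makes the catchment populations comparable in expectation. It does not do so for the people who later attend and are advised spectacles or surgery, because the intervention acts on who attends. If attendance goes from 7 to 14 per day, about half of the attendees at an intervention VC (7 of 14) are people who would not otherwise have come. From a start of 8 it is 6 of 14, or 43%. The added patients may differ in severity, felt need and ability to pay. Subtracting a baseline proportion does not remove this, because the mix changes during the intervention itself.

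The sustainability argument rests on volume: spectacles dispensed and surgeries done. A proportion conditional on advice does not rise with attendance, so it can move against the volume it is meant to represent. It can also improve when no patient of the usual kind has become more likely to accept treatment.

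**Working it through.** **The plan's own figure.** No figure is given for the uptake outcomes. The only sample-size figure is for attendance: 1.96² / 1² × 21 = 80.67, rounded up to 81 days. It reproduces, and is used below only as an observation period.

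**Inputs from the article.** Attendance of 7 per day at the intervention centers (Sample Size), 7-8 per day as baseline and 14 per day as target (Outcomes). Taking 7 per day for a control VC is an assumption.

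**Inputs not in the article.** The share of attendees advised and the uptake rates are assumed throughout.

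**Break-even.** With the same share advised, *a*, in both arms, the number dispensed per day is attendance × *a* × uptake.
- Control at 80% uptake, *a* = 30%: 7 × 0.30 × 0.80 = 1.68 per day.
- Intervention at 60%: 14 × 0.30 × 0.60 = 2.52 per day. The proportion is 20 points lower and the number is 2.52 / 1.68 = 1.50 times as large.
- Intervention at 40%: 14 × 0.30 × 0.40 = 1.68 per day, which is break-even.
- In general the count rises whenever intervention uptake exceeds 7/14 = 50% of control uptake. At 8 per day in control the threshold is 8/14 = 57%, so 80% could fall to just above 0.80 × 8/14 = 45.7%. The value of *a* cancels.

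**Mixture of usual and added patients.** Let A0 be advised with uptake p0 in the usual flow, and A1 advised with uptake p1 in the added flow.
- Arm proportion = (A0·p0 + A1·p1) / (A0 + A1). Count = A0·p0 + A1·p1.
- One VC, 81 days, 30% advised: A0 = A1 = 7 × 81 × 0.30 = 170.
- With p0 = 70% and p1 = 40%, control is 119 of 170 = 70%. Intervention is 119 + 68 = 187 of 340 = 55%. The proportion is 15 points lower and the count is 187 / 119 = 1.57 times as large.
- Range: advised share 20-40% in the usual flow and equal to that or 1.5 times it in the added flow, p0 of 50% or 70%, p1 of 30% to 50%. The count ratio runs from 1.43 to 2.50. The proportion runs from no change (50% in both flows) to a 24-point fall (70% to 46%).

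**The other direction.** With p0 = 50%, p1 = 70% and equal advised numbers, the intervention proportion is (0.50 + 0.70) / 2 = 60%. That is a 10-point gain produced wholly by the added patients, with no change in the behavior of the usual ones.

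**The case against.** The Outcomes sentence never uses the word proportion, rate or percentage. If advice must come before uptake, counting uptakes among the advised is the same as counting spectacles and surgeries delivered. That reading is possible, but a condition on those advised most naturally signals a denominator, and the sentence does not settle it. The article condenses a fuller protocol, yet this definition is stated in it and can be judged as stated.

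Four stronger readings are tempting, and the article does not support them.
- *Uptake will be measured only this way.* Data Analysis and the abstract can be read as covering counts, and the numbers behind both measures, along with revenue, will be collected.
- *Control VCs see mainly people who came on their own.* The Control Arm section and Table 1 provide for field referral there too. The contrast in case mix is one of degree, and no figure gives its size.
- *The intervention will look like a failure.* Direction is not fixed. Counselling, and free cataract services for those unable to pay, could raise uptake among the advised. The falls shown above come from assumed rates.
- *A significant loss would be declared.* The only named test concerns walk-in patients. Treating patients as independent, the 70% versus 55% example would give about 91% power for such a result. But no test of uptake is named, and there are only two VCs per arm, so that figure should not be relied on.

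It is also fair that attendance is the primary outcome, so a lower uptake share would be reported beside it. That limits the harm, but it does not make the conditional comparison interpretable.

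**Conclusion.** The point stands in this form: as worded, the secondary outcomes compare uptake within a group that forms after allocation and that the intervention is built to enlarge and reshape. A between-arm difference in that proportion is not protected by randomisation and could mislead either way.

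The conclusion rests on reading the sentence as a proportion and on the intervention changing who attends, which is its stated aim. The size cannot be fixed from the article. Break-even at half the control proportion needs only the 7 and 14 per day figures and an equal share advised. The 15-point and 20-point examples depend on assumed rates. Uptake among the advised remains a legitimate process measure. The fault is in letting it stand as the comparative outcome while the other sections leave the count undefined. This should be changed, but it concerns secondary outcomes and does not touch the primary one.

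**What to change.** Define the comparative secondary outcomes as the number of spectacles dispensed and the number of surgeries done per VC per open day. An alternative is per 1,000 population within 10 km, using the populations in Study Setting (about 70,000, 130,000, 111,000 and 110,000). Express each as change from the corresponding months a year earlier, net of the change in the control VCs. The Cost-Effectiveness Analysis section already does this for visits.

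Keep uptake among the advised as a descriptive process measure, reported by arm with its numerator and denominator and with no claim of effect. Align the abstract, Outcomes and Data Analysis sections so that each names the same measure in the same role.

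The cost is close to wording only. The VC management software supplies spectacles and the hospital's electronic records supply surgeries. The team should confirm that both can be extracted for the baseline months. The change does not address the separate limit of two VCs per arm.

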### Ethical Considerations

This study was approved by the institutional review board of [name] Eye Hospital (IRB/2020/APR/54), has been registered as a clinical trial (NCT04800718) [23], and will follow the tenets laid out in the Declaration of Helsinki. Protocol amendments will be shared with all relevant parties via email, and approval will be sought again.

Data will be encrypted and kept confidential. These confidential data will be anonymized, and personal data will only be visible to those responsible for implementation. The final data set will only be accessible to the research team. Trial results will be disseminated via publication.

## Results

Background work involved in planning the interventions and selecting VCs has been completed. Participant recruitment has begun and is currently in progress. We estimate the primary completion date (ie, the date on which participant enrollment ends) to be November 30, 2021, and the study completion date to be December 30, 2021.

## Discussion

### Importance of Principle Findings

To the best of our knowledge, there is no previous study assessing the impact of door-

to door intervention on the sustainability of VCs. VCs are evolving as an important model for primary eye care [7,10,19]. Any such model needs to be sustainable for it to be universally adopted. Uptake of glasses and uptake of surgery by patients are the major contributors to the sustainability of these VCs [24]. Both these parameters are dependent on the number of patients visiting the VC, and that will be assessed in our study.

### Addressing the Barriers to Uptake of Services

In their study describing barriers to the uptake of eye care services among the rural population, Marmamula et al [17] reported a lack of felt need as the most important person-related barriers. Thus, when designing our intervention package, we have included awareness generation as one of the key components. Other barriers detected in that population are the absence of someone to accompany, lack of accessibility, and affordability. Taking the preliminary screening to people’s doors in our intervention should manage, to some extent, the barriers to accessibility and the absence of an accompanist. We have also made the first examination at the VCs, free of cost for those reporting after a preliminary screening.

### Cost-Effectiveness of the Model

In addition to evaluating the effect on the number of patients visiting the VCs, our study will provide evidence for the cost-effectiveness of such an intervention. Although community engagement has been established as an important element of primary care [1], the evidence for the cost-effectiveness of a door-to-door screening model will help in decision making regarding the scalability of such an intervention.

### Generalizability of the Results

In India, like in many low-to-middle-income countries, the majority of the population resides in rural areas [25]. With an unequal distribution of doctors, including ophthalmologists, in rural locations [26], the need for primary care is greater there. All the VCs included in our study belong to such locations; thus, the learning can be used in other similar settings.

### Limitations

Although we randomly selected the VCs from our two operational regions, the fact that we operate only in North India can be one limitation of our study. We had planned this study before the COVID-19 pandemic, and even after reasonable delay due to the unrelenting nature of the pandemic, we plan to start this study during the ongoing pandemic. Due to this, the target for the number of patients visiting the VCs has reduced. Although the conditions may not be near normal during data collection, we do not anticipate any difference in the way in which the intervention and control VCs would be affected by the prevalent conditions. Due to the nature of the intervention, it is not possible to mask the personnel on ground, and this may bring in some short-term behavior change, which may not be sustained. Another limitation of our study would be the short duration of data collection following the intervention. To analyze the long-term impact of the intervention, another study will be planned subsequently in case the results of this study show a positive impact.

### Conclusion

We believe our results will provide evidence for the impact of the door-to-door screening model of community engagement, on VC sustainability. The cost-effectiveness analysis would help the community care organizations like us to decide the feasibility and scalability of such an intervention.

## Appendix

Multimedia Appendix 1 Data to be collected for the two study arms.

Multimedia Appendix 2 Data to be collected for calculating cost.

Multimedia Appendix 3 Data-monitoring committee.

## Abbreviations

CI: confidence interval
IEC: information, education, and communication
OPD: outpatient department
VC: vision center
VCMS: vision center management software
